## Abstract

**Background:**

Adolescents living with type 1 diabetes (T1D) often experience diabetes distress (DD), a construct distinct from depression or anxiety that refers to the negative emotions that arise from living with and managing diabetes. Self-compassion, which involves being open to one’s own suffering and treating oneself with the same care one would show to loved ones, is associated with better psychological and clinical outcomes among individuals with T1D. Self-compassion is a skill that can be taught and therefore represents an opportunity for intervention.

**Objective:**

The overall aim of this study is to assess the effectiveness of a web-based mindful self-compassion for teens (MSC-T) intervention on improving DD, anxiety, depression, diabetes-related disordered eating, and suicidal ideation experienced by youth with T1D (aged between 12 and 17 years) compared with a waitlist control group (standard of care). We will also explore (1) if the effect of the MSC-T intervention changes over time, (2) if the MSC-T intervention has a positive impact on measures of glycemic control, and (3) if the effect of the MSC-T intervention differs based on self-reported gender.

**Methods:**

We will conduct a single-center, parallel-group randomized controlled trial of 140 adolescents with T1D followed for 12 months. Participants will be randomly allocated (using hidden allocation) in a 1:1 ratio to either the MSC-T intervention or the waitlist control group. Our primary outcome is DD, as measured by the Problem Areas in Diabetes-Teen (PAID-T) version at 3 months. Secondary outcomes, assessed at 3 and 12 months, include anxiety (Generalized Anxiety Disorder 7-item [GAD-7] scale), depression (Patient Health Questionnaire-9 [PHQ-9]), diabetes-related disordered eating (Diabetes Eating Problem Survey-Revised [DEPS-R] version), and suicidal ideation (using 1 question from the PHQ-9).

**Results:**

Study recruitment began in October 2022 and was completed in March 2023, with a total of 141 participants enrolling. Data collection will be ongoing until March 2024. The first results are expected in June 2024.

**Conclusions:**

This study will be the first randomized trial to assess the effectiveness of the web-based MSC-T intervention on adolescents with T1D. Given that adolescence is a period where individuals are typically required to assume more responsibility for their diabetes care, providing adolescents with the tools they need to better manage the stress that often accompanies T1D management is paramount.

**Trial Registration:**

ClinicalTrials.gov NCT05463874; https://clinicaltrials.gov/study/NCT05463874

**International Registered Report Identifier (IRRID):**

DERR1-10.2196/53935

## Introduction

### Background and Rationale

Adolescence constitutes a critical developmental period during which youth establish their autonomy while grappling with the social, emotional, and physical challenges of becoming young adults. This period represents a time of tremendous vulnerability, during which psychiatric and mood disorders often manifest [1]. Adolescence is even more challenging for youth with type 1 diabetes (T1D), as they contend with the daily challenges of disease management in addition to the developmental challenges inherent to this phase of development.

Diabetes distress (DD) is an emotional construct that refers to the negative emotions that arise from living with and managing diabetes. The majority of youth with T1D experience some level of DD [2,3], with adolescent females experiencing greater DD than males [4-6]. More than one-third of youth with T1D suffer from substantial DD [7]. DD is apparent in youth for many reasons, including fear of stigma from peers [8], feeling overwhelmed by their diabetes regimen [9], and worry of hypoglycemia and long-term complications of a potentially fatal condition [9].

Self-compassion, a positive psychological construct, involves being open to one’s own suffering and treating oneself with the same care one would show to loved ones [10]. Youth can have varying degrees of innate self-compassion [11]. Higher levels of self-compassion are associated with lower levels of distress in youth with other chronic medical conditions [12], and it is a psychological characteristic that correlates with favorable outcomes, including psychological well-being, self-care, and hemoglobin A_1c_ (HbA_1c_) among individuals with diabetes [13].

Among adults with diabetes, an intervention to increase self-compassion resulted in reductions in DD [14]. However, this relationship has yet to be shown in youth with T1D. Self-compassion interventions lead to better psychological well-being and decreased psychopathology in healthy adolescents and those with some chronic conditions [15,16]. Since self-compassion is a modifiable behavior on which one can be trained [17,18], we have a largely untapped opportunity for intervention among youth with T1D.

Mindfulness-based therapy has led to short-term improvements in self-reported stress among adults and emerging adults with T1D [19]. However, a sole focus on mindfulness is not sufficient, as it does not provide enough training around active self-comforting in suffering. Mindfulness also does not provide the aptitude to address the feelings of failure and self-blame that are common among youth with T1D [20]. Therefore, our goal is to study the effects of a psychological intervention combining mindfulness and self-compassion (mindful self-compassion for teens [MSC-T]) on DD among youth with T1D.

### Objectives

Our primary objective is to compare DD at 3 months among youth with T1D who participated in the MSC-T intervention to those in a waitlist control group. Our secondary objectives are to (1) compare anxiety, depression, diabetes-related disordered eating, and suicidal ideation at 3 months among youth with T1D who participated in the MSC-T intervention with those in the waitlist control group; and (2) compare DD, anxiety, depression, diabetes-related disordered eating, and suicidal ideation at 12 months among youth with T1D who participated in the MSC-T intervention with those in the waitlist control group. Finally, our exploratory objectives are to (1) explore if the effect of the MSC-T intervention changes over time throughout the 12-month follow-up period, (2) compare glycemic control (HbA_1c_ and time in range) among adolescents with T1D who participated in the MSC-T intervention to those in the waitlist control group, and (3) explore if the effect of the web-based MSC-T intervention on DD differs based on self-reported gender.

### Hypotheses

We hypothesize that adolescents who participate in the MSC-T intervention will report lower DD, anxiety, depression, diabetes-related disordered eating, and suicidal ideation at 3 months compared with the waitlist control group.

## Methods

### Ethical Considerations

This study was reviewed and approved by the local Research Ethics Board at the Children’s Hospital of Eastern Ontario (CHEO; protocol 22/09E, approved July 17, 2022). Following an introduction from a member of the participant’s circle of care, in line with requirements outlined in the Personal Health Information Protection Act, a member of the research team will obtain written informed consent, either in person or remotely, using our REDCap (Research Electronic Data Capture; Vanderbilt University) system [21,22]. Participants will consent on their own behalf and will be compensated with gift cards for completing the study questionnaires (US $15 for baseline, US $20 for week 8, US $30 for month 3, US $30 for month 6, and US $35 for month 12) and up to 15 volunteer hours.

### Study Design

We will conduct a single-center, parallel-group randomized controlled trial assessing the effect of a web-based MSC-T intervention on DD in adolescents with T1D followed for 12 months, compared with a waitlist control group (standard of care).

### Participants and Recruitment

We will recruit 140 adolescents with T1D, aged between 12 and 17 years, from the Diabetes Clinic at CHEO in Ottawa, Ontario, Canada.

### Inclusion and Exclusion Criteria

The inclusion criteria and exclusion criteria for this study are presented in Textbox 1.

The inclusion and exclusion criteria.
**Inclusion criteria**
Aged between 12 and 17 years.Diagnosed with type 1 diabetes (T1D) ≥6 months before enrollment.Ability to provide informed consent.
**Exclusion criteria**
Inability or unwillingness to provide informed consent.Inability to speak English with enough fluency to complete all study-related tasks.Presence of an intellectual disability that would preclude participation in the mindful self-compassion for teens (MSC-T) intervention, as assessed by the treating physician.A lifetime diagnosis of a psychotic or bipolar disorder given by a clinician (these often involve intensive treatments with psychological and pharmacologic implications, which may confound our results).Presence of acute suicidality at the time of enrollment.Active participation in another mental health intervention trial.

### Trial Intervention

As shown in Figure 1, participants from the diabetes clinic at CHEO will be randomized to the MSC-T intervention group or the waitlist control group (standard of care).

**Figure 1 figure1:**
[figure not shown]
Schematic overview of the study. CHEO: Children’s Hospital of Eastern Ontario; MSC-T: mindful self-compassion for teens.

#### Intervention Group

The MSC-T intervention (Textbox 2) teaches the participants to be open to, rather than disconnected from, their own suffering and treat themselves with the same care they would show to a friend [10]. The program consists of 8 weekly interactive sessions, each lasting 1.5 hours (a total of 12 hours). The program will be led by our collaborators (KB and AL), who are trained, experienced MSC-T instructors. Each session will begin with a brief mindful art activity, which provides a transition to the class. Classes include developmentally appropriate hands-on exercises, videos, games, mindful movement, music meditation, and between-class practice assignments to solidify practices. The session content and structure were reviewed by our people with lived experience collaborators (SH and OI).

MSC-T program fidelity will be determined by (1) assessing the change in self-compassion between baseline and 8 weeks and (2) assessing if the required topics for each MSC-T session were covered and activities performed. Self-compassion will be assessed using the Self-Compassion Scale for Youth, a psychometrically valid and reliable measure of self-compassion for adolescents [23]. To ensure the respective topics are appropriately covered in the MSC-T sessions, a member of the study team will complete a fidelity assessment during each session.

Participants’ satisfaction and acceptability of the intervention will be evaluated using an intervention satisfaction survey, similar to what has been previously used to determine satisfaction with the web-based MSC-T program [18].

Program summary (sessions and topics) for mindful self-compassion for teens (MSC-T) intervention.
**Week 1**
Discovering mindful self-compassion: introduction to concepts of mindfulness and self-compassion; safety measures for class established; and both informal and formal practices are introduced.
**Week 2**
Paying attention on purpose: concepts of mindfulness, wandering mind, and default mode network are discussed; mindful eating, “soles of the feet,” and “palm of the hand” meditations are presented.
**Week 3**
Lovingkindness: “lovingkindness” is defined and lovingkindness practice is introduced; participants create their own lovingkindness phrases; adolescent brain development is discussed.
**Week 4**
Self-compassion: this exercise encourages teenagers to turn from the “inner critic” toward the “compassionate voice,” and music meditation is introduced.
**Week 5**
Self-compassion versus self-esteem: the difference between these 2 is elucidated, and the perils of social comparison are discussed.
**Week 6**
Living deeply: core values exercise; “giving and receiving” meditation is introduced.
**Week 7**
Managing difficult emotions: “soften, soothe, and allow” practice is introduced; tools to contend with anger and unmet needs are practiced; and 2 developing systems of the adolescent brain are explained.
**Week 8**
Embracing your life with gratitude: gratitude and self-appreciation practices are presented, and the wrap-up of the course takes place through writing a letter to oneself.

#### Waitlist Control Group

Participants in the wait-list control group will receive standard-of-care treatment as usual. Following the conclusion of the experimental protocol, participants in this group will be given the opportunity to complete the 8-week web-based MSC-T program.

### Randomization Procedures

We will use the randomization module in REDCap [21,22] to allocate participants to their group. The randomization table will be created by a study team member who is not directly involved in patient recruitment or data collection using R (R Core Team) [24]. The trial coordinator will generate the allocation for each participant following obtaining informed consent and completion of the baseline assessments (ie, there will be hidden allocation).

Participants will be randomly allocated to either the MSC-T intervention group or the waitlist control group using a 1:1 ratio block randomization. We will stratify each block by age group (12-14 years [early adolescence] or 15-17 years [middle adolescence]). The cohort will be divided by these age groups to deliver the intervention with the goal of fostering a developmentally appropriate and open environment. Stratification by age group is therefore necessary to ensure an equal age distribution between the treatment groups, since the developmental age of a participant could impact their response to the intervention [25]. We will also randomly vary the block size, with blocks of either 6 or 8, to prevent prediction of group allocation as participants are accrued [26].

### Data and Outcome Measures

We will collect the following demographic information at baseline: age, postal code (to determine socioeconomic status using neighborhood-level material and social deprivation indices [27,28]), optional self-reporting of gender identity (participants will be presented with a range of options [29,30]; Table 1), race or ethnicity, and indigeneity [31] (Table 2), and participant’s social context (living arrangements, etc). Medical history will be collected at baseline, and at intervals, it will be reviewed at each follow-up visit to determine if participants have been newly diagnosed with a serious mental illness (exclusion or withdrawal criteria).

**Table 1 table1:** Gender reporting options to be presented to participants. The presented gender reporting options are in line with accepted standards for determining gender identity in research [29,30]. Participants will be informed that the provision of this information is voluntary and that they will be allowed to select more than one.

Self-reported option	Analysis group
Male	Male
Female	Female
Transgender	Will depend on if another option is selected
Transgender boy or transgender male	Male
Transgender girl or transgender female	Female
Genderqueer	Gender diverse
Gender expansive	Gender diverse
Androgynous	Gender diverse
Nonbinary	Gender diverse
Two-spirited	Gender diverse
Third gender	Gender diverse
Agender	Gender diverse
Not sure or questioning	Gender diverse
Other	Will depend on free text
Prefer not to say	Will be excluded from gender analysis

**Table 2 table2:** Ethnicity and Indigenous identity questions and responses to be presented to participants. The categories are in line with accepted standards for reporting ethnicity from the Canadian Institute for Health Information [31]. Participants will be informed that the provision of this information is voluntary and that they will be allowed to select more than one. Participants will be asked to answer the following question: “In our society, people are often described by their race or racial background. These are not based in science, but our race may influence the way we are treated by individuals and institutions, and this may affect our health and health outcomes related to diabetes. Which category or categories best describe you? Check all that apply.”

Response category	Examples
Black	African, African Canadian, and Afro-Caribbean descent
East Asian	Chinese, Japanese, Korean, and Taiwanese descent
Indigenous (First Nations, Inuk/Inuit, Métis)	First Nations, Inuk or Inuit, and Métis descent
Latin American	Hispanic or Latin American descent
Middle Eastern	Arab, Persian, and West Asian descent (eg, Afghan, Egyptian, Iranian, Kurdish, Lebanese, and Turkish)
South Asian	South Asian descent (eg, Bangladeshi, Indian, Indo-Caribbean, Pakistani, and Sri Lankan)
Southeast Asian	Cambodian, Filipino, Indonesian, Thai, Vietnamese, or other Southeast Asian descent
White	European descent
Other category	Includes options not described above
Do not know	N/A^a^
Prefer not to answer	N/A

^a^N/A: not applicable.

Our primary outcome, DD, has been shown to be the psychological construct most related to metabolic outcomes in adolescents with T1D [3]. DD will be measured using the Problem Areas in Diabetes-Teens (PAID-T) version [32], a validated measure to evaluate diabetes-specific emotional distress in adolescents with high internal consistency (Cronbach α=.96) [32]. It consists of 26 items, each scored on a 6-point ordinal scale, allowing for the calculation of an overall distress score of 26-156, with scores of <70, 70-90, and >90 representing none-to-mild, moderate, and severe DD, respectively [33]. The PAID-T has excellent psychometric properties [34], is sensitive to change from behavioral intervention [35], and is a commonly used measure to assess DD in adolescents [7,36].

Our secondary outcomes are anxiety, depression, diabetes-related disordered eating, and suicidal ideation. Symptoms of anxiety will be measured using the Generalized Anxiety Disorder 7-item (GAD-7) scale, a self-report tool to detect clinically significant anxiety symptoms. The GAD-7 is scored from 0-21, with 0-4, 5-9, 10-14, and 15-21 indicating minimal, mild, moderate, and severe anxiety symptoms, respectively [37]. It has been validated in adolescents [38] and has previously been used to assess adolescents with T1D [39,40].

Symptoms of depression will be measured using the Patient Health Questionnaire-9 (PHQ-9) by self-report [41]. The PHQ-9 is a valid and reliable screening tool for identifying adolescents meeting the Diagnostic and Statistical Manual of Mental Disorders, Fourth Edition (DSM-IV) criteria for major depression [41]. Scores range from 0-27, and in adolescents, scores of 0-4, 5-10, 11-14, 15-19, and ≥20 indicate absence of, mild, moderate, moderately severe, and severe depression, respectively [41].

Symptoms of diabetes-related disordered eating will be measured using the Diabetes Eating Problem Survey-Revised (DEPS-R) version [42], a diabetes-specific measure of disordered eating symptoms that is valid for use in adolescents with T1D [42]. The DEPS-R is scored from 0-80, with higher scores indicating more disordered eating behaviors, and a score of ≥20 is suggestive of disordered eating behaviors [42]. The use of a diabetes-specific tool to measure disordered eating is important, as generic measures may overestimate the prevalence of disordered eating symptoms given that diabetes management involves an emphasis on food intake and carbohydrate counting and that insulin restriction is not captured in generic measures [43].

Suicidal ideation will be assessed using 1 question on the PHQ-9, which asks the respondent if they have had thoughts that they would be better off dead or of hurting themselves in the previous 2 weeks. This question is scored on a scale from 0 (not at all) to 3 (nearly every day). In line with previous use of the PHQ-9 [44], we will consider any score of >0 to be indicative that suicidal ideation is present.

Our exploratory outcomes are the effects of time, HbA_1c_, time in range, and effect of gender. We will assess whether the effect of the MSC-T intervention on DD changes over time by exploring the interaction of time (ie, study time point) with DD. We will assess both HbA_1c_ and time in range, as not all our clinic patients wear a continuous glucose monitor (CGM), which is necessary to calculate time in range (>70% of our clinic patients wear a CGM).

HbA_1c_ is a measure of the average blood glucose levels over the previous 3 months and is a routinely followed biochemical marker used to gauge metabolic control in individuals with T1D. We will explore changes in HbA_1c_ over the duration of our trial, as mental health morbidity has been associated with higher HbA_1c_ levels [45,46]. Time in range is a metric that denotes the proportion of time that a person’s glucose level is within a desired target range, calculated using a CGM. A total of 14 days of data from CGM provides a good approximation of glucose data [47]; time in range will allow us to evaluate the glucose control at the various time points. We will collect CGM data at all study visits. Given the web-based nature of the trial combined with the high proportion of our clinic population that uses CGM, which is a more reliable measure of metabolic control [48], we will minimize additional blood collection by recording results from clinically collected HbA_1c_ at baseline and 1 year.

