### Safety Parameters and Description of Risk

All the mental health outcomes being assessed are self-reported by participants directly into the study database. The principal investigator or delegate and study coordinator will be immediately alerted through an automated REDCap algorithm when (1) an individual self-reports as having suicidal ideation >0 on question 9 of the PHQ-9 or (2) an individual intentionally does not fill out the suicidality question on the PHQ-9. The principal investigator, delegate, or study coordinator will contact the participant’s endocrinologist or the endocrinologist on call, who will conduct a same-day risk assessment using the Ask Suicide-Screening Questionnaire (ASQ) [49]. If the participant is judged to have acute suicidality or suicidal ideation as per the ASQ, the assessor will either suggest a referral to the emergency department or contact the psychiatrist on call, who will suggest clinical follow-up as appropriate. The assessor will report the results of the ASQ screening back to the study coordinator within 1 day. Participants with acute suicidality as per the ASQ will then be excluded or withdrawn from the study.

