#### Statistical Analysis

For the MSC-T and waitlist control groups, the following will be summarized using descriptive statistics: participant baseline characteristics, mental health outcome measures, and self-compassion score responses from each study time point, and for the MSC-T group, we will summarize the results of the intervention satisfaction survey and session attendance.

Our main analyses will be performed based on the intention-to-treat principle. We will also complete per-protocol analyses where we will exclude participants based on nonadherence to the intervention (defined as attending fewer than 6 out of 8 MSC-T sessions, in line with previous work done using MSC-T [56]).

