### Strengths and Limitations

To our knowledge, this is the first randomized controlled trial using the MSC-T intervention to address DD in adolescents with T1D. One of our instructors (KB) is a person with lived experience of T1D; having an instructor who is also a person with lived experience of the condition has been identified as a key component in previous studies using MSC interventions [56]. The longer-term follow-up of 12 months is also a clear strength. Throughout adolescence, youth are typically required to become more independent with their diabetes self-management while receiving diminished support from their caregivers. Mental health morbidity, including DD, is associated with poor glycemic control, diabetic ketoacidosis, and hypoglycemia in youth with T1D [7,65,66]. The MSC-T program will help adolescents with T1D develop skills to better cope with their emotions around managing their diabetes.

There are, however, some potential limitations to this study. The trial is single-blind; participants and the trial coordinator are not blinded to their assignment group. However, the statistician conducting the primary analysis will be blinded to participant allocation to the MSC-T intervention or waitlist control group. Given that the intervention is web-based, it does require the use of high-speed internet and a device that has webcam functionality, which may make it difficult for some youth to attend should these items be lacking. However, in Canada and the United States, over 96% [67] and 95% [68] of youth and emerging adults own smartphones, respectively, suggesting that if the program were to be scaled nationally or internationally, attending such a program would be feasible for the majority of North Americans.

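### The follow-up withdrawal criterion uses an undefined term that differs from the entry exclusion and, on either reading, can remove randomised participants for a post-randomisation event

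*Protocol article*

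**What the plan says.** In the protocol article, Data and Outcome Measures says that medical history is to be "reviewed at each follow-up visit to determine if participants have been newly diagnosed with a serious mental illness (exclusion or withdrawal criteria". The schedule of activities (Table 3) places this review at baseline and at 8 weeks, 3, 6 and 12 months.

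The exclusion criteria in Textbox 1 list one psychiatric diagnosis: "A lifetime diagnosis of a psychotic or bipolar disorder given by a clinician". The reason given is that the intensive treatment of these disorders may confound the results. A separate item reads "Presence of acute suicidality at the time of enrollment". Depression, anxiety and eating disorders are not grounds for exclusion at entry.

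Safety Parameters and Description of Risk has its own rule for suicidality: "Participants with acute suicidality as per the ASQ will then be excluded or withdrawn from the study".

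On outcomes, the article states: "Our secondary outcomes are anxiety, depression, diabetes-related disordered eating, and suicidal ideation". On analysis, it states: "Our main analyses will be performed based on the intention-to-treat principle".

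Trial Management assigns the interim history review to the study coordinator. Strengths and Limitations says that "participants and the trial coordinator are not blinded to their assignment group".

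**The concern.** The follow-up review applies a criterion after randomisation, and words it differently from the entry criterion. Two staff members could reasonably disagree on whether a new diagnosis of major depression at 8 weeks is covered.

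The larger issue is what follows from a new diagnosis. At entry, excluding a diagnosis only defines the population. After randomisation, a new diagnosis may depend on the arm, either through an effect of the programme or because weekly contact changes how readily a problem comes to light. Removing people on that basis breaks the balance that randomisation gave. If those removed are high scorers and more of them are controls, the control mean falls and a benefit of MSC-T is understated. If more of them are in the MSC-T arm, the benefit is overstated.

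**Working it through.** **1. The passages side by side**

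| Place | Condition | When | Consequence |
|---|---|---|---|
| Exclusion criteria | Psychotic or bipolar disorder, diagnosed by a clinician | Entry | Not enrolled |
| Data and Outcome Measures | New *serious mental illness* (undefined) | Each follow-up visit | Exclusion or withdrawal |
| Safety Parameters | Acute suicidality on the ASQ | After an alert | Excluded or withdrawn from the study |

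The second and third rows pair exclusion with withdrawal in the same way. The third says outright that the withdrawal is from the study. The natural reading of the second is therefore leaving the study, not merely stopping sessions.

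The two withdrawal rules have different triggers. The suicidality rule starts from an alert when "an individual self-reports as having suicidal ideation >0 on question 9 of the PHQ-9", or when that question is deliberately left blank, and then depends on the ASQ. The rule discussed here starts from a diagnosis in the medical history, so settling one leaves the other untouched.

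**2. The two readings**

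- Narrow: the parenthesis points back to Textbox 1, so only a new psychotic or bipolar diagnosis counts. Neither is a trial outcome.
- Wide: the ordinary meaning of the term applies, which can include severe depression or an eating disorder. These overlap with the PHQ-9 and DEPS-R outcomes.

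The text does not decide between them. On both, removal follows randomisation.

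**3. Does the missing-data plan repair it?**

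The best-case and worst-case imputation is headed as a sensitivity analysis. It covers only participants with at least one available data point, and both scenarios are defined by PAID-T improvement. It does not restore removed participants to the main analysis, and it describes no scenario for the other outcomes.

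**4. Size**

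The article gives no rate of new diagnoses or of such withdrawals, and its 30% attrition allowance is not split by cause. There is no figure to reproduce, so what follows is an illustration.

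Shift in the contrast ≈ (k / n) × e, where:

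- n = 70 per arm (Sample Size section);
- k = difference between arms in the number removed;
- e = assumed excess of a removed participant over the arm mean, 30 to 40 PAID-T points. Against the planning control mean of 73 this is a score of 103 to 113, in the article's severe band (above 90).

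For k = 1:

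- 1/70 × 30 = 0.43 points; 1/70 × 40 = 0.57 points.
- Against the 12-point target: 0.43/12 = 3.6%; 0.57/12 = 4.8%.

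Which k is plausible on the wide reading? Assume that 2% to 6% are newly diagnosed over 12 months:

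- 141 × 0.02 = 2.8; 141 × 0.06 = 8.5 participants over the year.
- With even accrual, a quarter of these by 3 months: about 0.7 to 2.1 in total.
- Two removals by 3 months, both in one arm: 2/70 × 30 = 0.86; 2/70 × 40 = 1.14 points.
- A three-person imbalance by 12 months: 3/70 × 30 = 1.29; 3/70 × 40 = 1.71 points.

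On the narrow reading I assume 0 or 1 removals in total. The primary model adjusts for baseline distress, which would absorb part of the excess of someone already scoring high at entry. The figures above ignore this and so lean high.

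**The case against.** The strongest case on the other side is that the parenthesis refers to the exclusion list, and the only psychiatric diagnosis there is psychotic or bipolar disorder. The stated rationale about intensive treatment fits that shorthand, and no passage names depression, anxiety or an eating disorder as a ground for withdrawal. This stands. A reader might infer that the criterion is wider than the entry exclusion, that the two passages contradict each other, and that the trial removes participants for developing the conditions it measures. The documents support none of these as fact; they show only that the terms differ and that the wide reading is open.

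A reader might also infer that an unblinded coordinator judges who is removed. The article asks whether a diagnosis has been made, and the entry criterion requires a clinician's diagnosis. The coordinator records it. The article also does not say that the study coordinator and the trial coordinator are the same role, though they appear to be.

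It can further be said that a condensed article may leave the definition to the full protocol. That is fair, and the missing definition alone would not be a finding. The point rests on what the article does state: a post-randomisation criterion in terms that do not match its own eligibility list.

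Finally, the article does not say that outcome collection stops at withdrawal, and it commits to intention-to-treat. This tempers the conflict but does not remove it. Withdrawal in its ordinary sense ends follow-up, and the neighbouring suicidality rule makes that sense explicit.

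**Conclusion.** The point holds in a limited form. The follow-up criterion and the entry exclusion use different terms and need reconciling. Whichever meaning was intended, the wording lets a randomised participant leave the study because of an event that the arm may affect. That conflicts with the intention-to-treat principle, and the missing-data sensitivity analysis does not cure it.

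The likely effect is small. It is probably negligible on the narrow reading. On the wide reading it is about 0.4 to 0.6 PAID-T points per one-person imbalance at 3 months, or roughly 4% to 5% of the 12-point target, with more scope by 12 months. These figures rest on the assumed 30 to 40 point excess and on 70 analysed per arm; none of the removal rates comes from the documents. The three-person figure of 1.3 to 1.7 points should not be read as a bias in the primary outcome. It presumes a 12-month imbalance larger than all the removals expected by 3 months under the same assumptions, whereas the 12-point target belongs to the 3-month endpoint.

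**What to change.** - Reconcile Data and Outcome Measures with Textbox 1, using one defined term in both places.
- State that a new diagnosis after randomisation does not by itself end outcome collection. The participant continues the scheduled questionnaires unless consent is withdrawn, and is analysed in the arm assigned.
- Report new diagnoses, and any resulting withdrawals, by arm and visit.

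Whether sessions or other treatment continue after a new diagnosis is a clinical decision for the sponsor, and nothing here proposes a rule for it.

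The cost is a short amendment. The questionnaires are already scheduled for every participant in Table 3, are entered by participants directly into the study database, and carry compensation that is already planned. If follow-up has ended, the reporting by arm can still be done from the case report forms.
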